### Masking

Professionals implementing the intervention are not blinded to the assignment group. However, data extraction will be performed centrally by computer technicians not involved in the study and data will be treated by research personnel after anonymisation.

### Analysis

Data will be extracted from centralized computerized medical records. Analysis will be performed at the PCU level taking the cluster design into account [32]. Indicators will be obtained for each PCU before and after the intervention and the differences will be weighted by cluster size. All analyses will be performed using Student’s *t*-test as implemented in SPSS 19. A secondary multi-level analysis will be performed using MLwiN (version 2.21) to determine the intracluster correlation coefficients (ICCs).

Analysis will be performed on an intention-to-treat basis.

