## Methods/Design

### Study design and setting

This study is a cluster randomized trial conducted in two urban primary care districts in the Basque Health Service (Ekialde and Bilbao). These districts cover 36.9% of the population in the Basque Country. Primary care units (PCU) will be randomly assigned.

A cluster-type design is selected as the intervention was aimed at professionals working in a PCU and due to the risk of contamination between professionals working in the same PCU [27,28].

A repeated cross-sectional design is used for all patients who attend during the baseline period (pre-intervention, or “PRE”) and in the post-intervention period (“POST”), with different samples. Such an approach is appropriate when the aim of the study is to determine the impact of CPG implementation on the population and provides greater long-term power [27,28]. It also allows minor baseline differences that may arise due to cluster randomization to be compensated. The study design is shown in Figure 1.

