### Sample size

The following aspects were taken into account when calculating the sample size:

• On average, 45-50% of diabetic patients assigned to a healthcare professional undergo at least two annual HbA1c analyses (standard deviation 15-20%). An annual analysis is requested in around 35% of hypertensive patients. (Data taken from the Provider Agreement, 2007).

• From a clinical and operational viewpoint, an intervention strategy would be worthwhile if these averages could be increased to 55-60% for diabetes and 43% for hypertension.

• The size of the PCUs is similar, with around 10 physicians per PCU, and the number of patients assigned to each clinician is also similar.

• The intracluster correlation coefficient (ICC) is 0.10 [29-31].

In light of these considerations, approximately 100 physicians per group (10 PCUs in each group) would be needed for an α of 0.05 and a β of 0.20. Applying the cluster-related design effect gives a final number of 20 PCUs per group (intervention and control).

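### The planned t-test on PRE-POST differences is valid but less precise than adjusting POST for PRE, and the stated 80% power does not automatically carry over to it

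*Protocol article*

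**What the plan says.** The Analysis section describes the primary comparison in two sentences: "Indicators will be obtained for each PCU before and after the intervention and the differences will be weighted by cluster size" and "All analyses will be performed using Student’s *t*-test as implemented in SPSS 19". A t-test takes no covariate, so the natural reading is that each PCU's POST minus PRE difference is compared between arms without adjustment. The only model mentioned has another purpose: "A secondary multi-level analysis will be performed using MLwiN (version 2.21) to determine the intracluster correlation coefficients (ICCs").

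Study design and setting gives a reason for collecting PRE data: "It also allows minor baseline differences that may arise due to cluster randomization to be compensated". It also says that the PRE and POST samples differ.

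The Sample size section states that about 100 physicians per group "would be needed for an α of 0.05 and a β of 0.20", and then 20 PCUs per group after the design effect. Its inputs describe one point in time. For diabetes, 45-50% of patients "undergo at least two annual HbA1c analyses (standard deviation 15-20"%). For hypertension, "An annual analysis is requested in around 35% of hypertensive patients", with no separate SD. An intervention is judged worthwhile "if these averages could be increased to 55-60% for diabetes and 43% for hypertension". No PRE-POST correlation appears.

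**The concern.** With 43 PCUs as the units of analysis, precision at PCU level is the scarce resource, and adding patients within PCUs does little for it. The PRE indicator is already collected, and there are two ways to use it. Subtraction fixes the coefficient on PRE at 1. Regression estimates that coefficient from the data. Unless the true coefficient is 1, subtraction adds noise. If PRE predicts POST only weakly, the result is less precise than leaving PRE out.

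This also touches the stated purpose of the PRE data. When the arms differ by chance at baseline, only about r times that difference is expected to persist (equal variances), yet the change score removes all of it. Regression removes the part that the data support.

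Finally, the trial appears to have been sized for a comparison other than the one it plans, so the stated power holds for the planned test only under a condition on r that the article does not give.

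**Working it through.** **Inputs.** From Sample size: 8-point effect for hypertension (35% to 43%), 10-point effect for diabetes, SD 15-20 points (given for diabetes), 10 physicians per PCU, ICC 0.10, 20 PCUs per group, α 0.05, power 0.80. From Study population: 43 PCUs randomized. Assumed: two-sided α; SD 20 for hypertension; a 21/22 split; equal PRE and POST variances; equal PCU sizes (the article calls them similar); r, which is varied.

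**Reproducing the plan.** Physicians per group, single time point: 2 × (20/8)² × (1.960 + 0.842)² = 98.1, so 99 against the stated 100 or so. Design effect: 1 + 9 × 0.10 = 1.9. Then 99 × 1.9 = 188 physicians, or 19 PCUs per group against the stated 20. The PCU-level SD is 20 × √(1.9/10) = 8.72. Power for POST alone with 20 per group (noncentral t, 38 df) is 80.7%. The calculation needs no PRE-POST correlation, so the stated 80% belongs to a POST-only comparison.

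**Variance relative to POST alone.**
- Change score: 2(1 − r)
- Regression on PRE (ANCOVA): 1 − r²
- Ratio, ANCOVA to change score: (1 + r)/2, which is 0.65 at r = 0.3, 0.75 at 0.5 and 0.85 at 0.7
- The change score exceeds POST alone when 2(1 − r) > 1, that is, when r < 0.5

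**Power, hypertension, 8 points, SD 20, PCUs 21/22.** Noncentral t with 41 df for the change score. ANCOVA uses 40 df, with its variance multiplied by 1 + 1/39 for estimating the slope. POST alone gives 83.6%.

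| r | Change score | ANCOVA |
|---|---|---|
| 0.3 | 69.9% | 86.0% |
| 0.4 | 76.5% | 88.5% |
| 0.5 | 83.6% | 91.7% |
| 0.7 | 96.6% | 98.2% |

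**Value of r below which change-score power drops under 80%.**

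| Effect, SD | 20/20 | 21/22 |
|---|---|---|
| 8 points, SD 20 | 0.49 | 0.45 |
| 8 points, SD 17.5 | 0.33 | 0.28 |
| 8 points, SD 15 | 0.09 | 0.02 |
| 10 points, SD 20 | 0.20 | 0.14 |
| 10 points, SD 17.5 or 15 | none at r ≥ 0 | none at r ≥ 0 |

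**What the plan's inputs suggest about r.** With SD 20 and ICC 0.10, the variance of a PCU mean is 40 between PCUs plus 360/10 = 36 within, 76 in all. If the PCU component persists fully and physicians' deviations do not persist at all, r = 40/76 = 0.53. Change-score power is then about 83% at 20/20 and 86% at 21/22.

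**The case against.** The strongest reply is that nothing here is invalid. Under randomization the change-score t-test is unbiased and keeps its type I error, and on average it does compensate baseline differences, as the design section intends. That stands. The over-correction matters only conditionally, once an imbalance has been observed.

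The second reply is that the power loss needs unfavourable inputs: the top of an SD range stated for another endpoint, and an r below the 0.53 that the plan's variance components give if PCU practice persists. Persistence in physicians' habits would raise r further. That largely stands too. A reader might infer that the trial is underpowered, but the documents do not support this: r is not given, 43 PCUs were randomized rather than 40, and the shortfall concerns the 8-point effect far more than the 10-point one. Equally, nothing in the article shows that r is high. The 0.53 is itself conditional, and r would be lower if practice within PCUs shifts between periods.

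A reader might also infer that ANCOVA can never do worse. With few clusters that is not quite so. At r = 0 and 20/20, the cost of estimating the slope brings ANCOVA to 79.6%, against 80.7% for POST alone.

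The last reply is that an article leaves model details to a fuller plan. Here that carries little weight, because the article names the t-test for all analyses.

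**Conclusion.** The point holds as one of efficiency and of a mismatch with the basis of the sample size, not of validity. For the same data, regression on PRE has (1 + r)/2 of the change-score variance, less a small cost for the slope. The gain is large at low r (about 16 points of power at r = 0.3) and small at high r (under 2 points at r = 0.7).

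The stated 80% is not assured for the planned test. At SD 20, the 8-point hypertension effect falls short only if r is below about 0.45 with 43 PCUs, or 0.49 with 20 per group. At SD 17.5 the limit is about 0.28 to 0.33. At SD 15, and for the 10-point diabetes effect, r would have to be much lower, or no shortfall occurs at any r of 0 or more. Cardiovascular risk assessment, the third primary endpoint, has no target or SD in the Sample size section, so its power cannot be computed.

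All power figures rest on an unstated r, equal PRE and POST variances, an assumed hypertension SD and an assumed 21/22 split. The variance comparison is firm; the size of the power loss is not.

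**What to change.** For each primary endpoint, make the primary analysis a PCU-level linear regression of the POST indicator on arm and the same PCU's PRE indicator. Keep the cluster-size weights already planned. Report the adjusted difference with a 95% confidence interval from the residual degrees of freedom, counted in PCUs (43 − 3 = 40). Retain the t-test on differences as a sensitivity analysis. State in the Sample size section that the calculation is for a single time point.

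The cost is a change of wording and one degree of freedom; the data are already to be extracted. Adding district as a covariate is optional and not part of this change, since no gain from it has been shown.

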## Discussion

There is a growing need to identify effective implementation strategies for CPGs for the management of cardiovascular risk factors in primary care. This study is one of the few cluster randomized trials concerning the implementation of clinical practice guidelines in Spanish primary care.

This study focuses on multiple cardiovascular risk factors as primary endpoints. Its pragmatic design is aimed at determined the actual impact of implementing CPGs for type 2 diabetes, hypertension and dyslipidemia via a multifaceted intervention based on identifying local barriers to CPG implementation, and it is aimed at primary care professionals.

The limitations of this study include the use of medical records as data source. Giving the nature of the study, the intervention cannot be masked.

The findings of this study will allow a more effective CPG planning in the primary cardiovascular care field to be designed. Similarly, it will allow the key aspects of recommendation implementation in our setting to be identified. All this information may prove useful in the organisational transformation currently underway in the Basque Country to adapt the health system to the care needs of patients with chronic diseases.

## Abbreviations

CPG: Clinical Practice Guideline; HbA1c: glycosylated hemoglobin; ICC: Intracluster Correlation Coefficient; PCU: Primary Care Unit.
